## Concomitant treatments

Rifampin may accelerate the metabolism and reduce the activity of many co-administered drugs. The treating team will evaluate possible interaction with concomitant medications pre-randomization (baseline) and at each follow-up visit and judge if the potential interaction is manageable or not. If an interaction is judged not manageable by the treating team, and if treating team or participant does not wish to change the concomitant medication, the treatment with rifampin will be stopped (or not started). If this is decided before randomization, the participant will not be enrolled in the study (as per exclusion criteria, see page 17), and will be offered alternative treatment and follow up for latent TB. If a new medication is started after randomization and during treatment phase, then the study drug (rifampin) will be permanently stopped. This will be reported as an adverse event (as per protocol definition) and the participant will be offered alternative treatment (such as INH) and follow-up for latent TB. Discussions about alternative treatment and follow up will be individualized by the treating team.

As a guide, a partial list of drugs with important interactions with rifampin is included in appendix 1 of this protocol. But, at any time during the trial, there may be other, new concomitant medication taken by participants, which are not included in this list. Therefore, any new medications should be checked – by pharmacists at the site, or the trial coordination center – for potential interactions.

## Population and eligibility criteria:

Study sites: Calgary, Edmonton, Montreal and Greater Vancouver (Canada); Bandung (Indonesia), and Ho Chi Minh City (Vietnam).

Participants: Potentially eligible participants are adults and children aged 10 and older, who are eligible to take LTBI treatment according to Canadian guidelines in the Canadian sites, and according to WHO guidelines in the international sites. All eligible persons must have evidence of latent TB infection defined as a positive tuberculin skin test (5mm or greater or 10mm or greater, based on National guidelines) or positive interferon gamma release assay, and active TB has been excluded. Eligible persons will include household contacts of newly diagnosed patients with active microbiologically confirmed pulmonary TB, or with other risk factors, including HIV infection, other causes of immune suppression (see <https://bmjopen.bmj.com/content/6/11/e013488> for a detailed list), and fibronodular disease on chest-x-ray (CXR). Household contacts will be defined as having slept in the same house at least one night per week or spent at least 5 hours per week visiting the house, on average, over the last 3 months prior to the diagnosis of the index TB patient.

### Inclusion criteria:

1. Adults, and children aged 10 and older (see rationale for exclusion of younger children below) who weigh at least 25kg.
2. Evidence of latent TB infection: positive tuberculin skin test (5mm or greater or 10mm or greater, based on National guidelines) or positive interferon gamma release assay.
3. Eligible to take latent TB treatment according to Canadian guidelines in the Canadian sites, and according to WHO guidelines in the international sites. This include household contacts, other contacts, HIV infected, other causes of immune suppression, fibronodular disease on CXR, or other indication.

### Exclusion criteria:

1. Children aged 0-9 and children aged 10 or older who weigh less than 25kg
2. Pregnancy
3. Baseline AST or ALT that is at least 3 times higher than upper limit of normal
4. Baseline Grade 3-4 abnormalities of hematological tests (WBC, platelets or hemoglobin)
5. Prior treatment for latent or active TB.
6. Rifampin contra-indicated – due to potential drug interactions that are considered too important, or difficult to manage, by health care provider; or due to history of allergy/ hypersensitivity to rifampin, rifabutin or rifapentine.
7. Household contacts of index TB patients with confirmed, or suspected rifampin resistant TB will be excluded.

In centers where culture and drug sensitivity testing is routinely performed for all patients with active TB, then the index TB patients must have rifampin sensitive TB.

In settings where phenotypic drug susceptibility testing (DST) are not available, but GeneXpert is available, then the index patients must have a GeneXpert result predicting rifampin susceptibility.

If neither DST nor GeneXpert are available, then the index TB patients must have no prior TB therapy (i.e. **new** case) to reduce the probability of drug resistance. (In the two international sites the prevalence of rifampin resistance (MDR or RR) among previously untreated patients with newly diagnosed active pulmonary TB (new cases) is respectively 4.1% in Vietnam and 2.4% in Indonesia (according to WHO Country profile, 2017).

Note: In settings with phenotypic DST, household contacts may be enrolled and randomized before the DST results are available, as long as the index TB patient is not expected to have drug resistant TB. If a HHC is enrolled and later the DST reveals rifampin resistance in their index TB patient, they can be excluded post-randomization.

Valid exclusions post-randomization:

In settings where the results of required laboratory tests are not available on the same day, participants, without a history of liver or hematological disease, may be randomized before all test results are known. In this situation, randomized participants will be informed that they should NOT start therapy until they are informed by research staff that their initial laboratory test results are normal. If any of the lab tests are abnormal, and exceed levels specified in the study’s exclusion criteria (for example, liver transaminases are more than 3 times upper limit of normal, or pregnancy test is positive), participants will be told not to start the study medication and will be excluded per protocol post-randomization. In this situation the coordinating center will be informed, and participants will be referred back to the treating team for re-assessment. If the treating team decides to give LTBI treatment, medications and all follow-up will be given through routine care.

In patients with history of liver or hematological disease the lab test results must be available before randomization.

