## Pre-treatment:

Potential participants who may meet the eligibility criteria will be asked by the treating team, if they would like to meet research staff. Those who are not interested in participating will receive standard care from the treating team. For those who accept to meet with study team, their eligibility criteria will be checked and those who are eligible will be asked to provide informed consent. For those who consent a baseline evaluation will take place. In this baseline evaluation, all usual clinical and demographic information will be collected including indication for LTBI treatment (i.e. risk factors as being a close household contact, having immunosuppression, etc).

A close household contact (HHC) will be defined as persons who, over the past 3 months, slept in the same house at least one night per week, or spent at least 5 hours per week in the same house as a patient with newly microbiologically diagnosed active pulmonary TB (index TB patient). In sites in which DST or GeneXpert is done routinely for pulmonary TB patients, DST or GeneXpert results for rifampin for the index patient of each HHC will also be recorded.

Prior to enrolment all potential participants must have no symptoms suggestive of active TB, a chest x-ray (within a maximum of 6 months from the date of enrolment) that is considered to have no evidence of active TB, and a positive TST or IGRA as defined above. If the potential participants have abnormalities on chest X-ray, or TB symptoms, they will undergo investigation including sputum AFB smears/ TB cultures and/or GeneXpert. If these investigations to exclude active TB are negative, then they will be eligible for enrolment.

A pregnancy test will be performed prior to enrolment for all women of child bearing potential, unless the treating team judges it is not appropriate. For adolescents, results of pregnancy test will be disclosed to participants who are 14 years old or older and to participants and caregivers if less than 14 years old. Participants who are found to be pregnant will not be enrolled in the study, but an alternative individualized plan for LTBI management will be discussed with treating team and patients.

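### The rule on rifampin-resistant index TB names only household contacts, although other contacts are eligible and the analysis section removes contacts in general

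*Protocol*

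**What the plan says.** Inclusion criterion 3 lists the indications that qualify a person for the trial: "This include household contacts, other contacts, HIV infected, other causes of immune suppression, fibronodular disease on CXR, or other indication". Household contacts and other contacts are thus two groups.

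Exclusion criterion 7 states: "Household contacts of index TB patients with confirmed, or suspected rifampin resistant TB will be excluded". Three sub-paragraphs follow, by setting. Where culture and susceptibility testing are routine, "then the index TB patients must have rifampin sensitive TB". Where only GeneXpert is available, it must predict susceptibility. Where neither exists, the index patient must be a new case. A closing note lets household contacts be randomized before the susceptibility result and adds: "If a HHC is enrolled and later the DST reveals rifampin resistance in their index TB patient, they can be excluded post-randomization".

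Under Pre-treatment, the protocol says that "DST or GeneXpert results for rifampin for the index patient of each HHC will also be recorded". The same section defines a household contact as someone who "slept in the same house at least one night per week, or spent at least 5 hours per week in the same house" as the index patient.

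The Statistical analysis section, under the primary completion analysis, describes a modified intention-to-treat population without the valid post-randomization exclusions. Its example is contacts whose index case is later found resistant to rifampin. It does not say household contacts.

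**The concern.** The sponsor judged that a person presumably infected by a rifampin-resistant strain should not enter a trial in which every arm is rifampin alone, and wrote a rule to that effect. The reason for the rule is the exposure, and it applies equally to someone exposed at work or at school. As worded, the rule stops at the household.

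Two things are at stake. The first is participant protection: a non-household contact of a known or suspected resistant case can satisfy every written criterion. The second is the definition of the primary analysis population. Part of the trial is open-label (duration is known to participants and staff), so post-randomization removal should follow one unambiguous rule. Here the answer for a non-household contact depends on which section is followed.

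**Working it through.** No power or sample-size figure is involved. The check is a comparison of the texts, followed by a rough scale.

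**Which contacts each section covers**

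| Place in the protocol | Contacts covered |
| --- | --- |
| Inclusion criterion 3 | Household contacts and other contacts, both eligible |
| Exclusion criterion 7, opening sentence | Household contacts |
| Exclusion criterion 7, sub-paragraphs | Index TB patients, under the household-contact heading |
| Exclusion criterion 7, closing note | Household contacts |
| Pre-treatment, recording of index result | Household contacts |
| Statistical analysis, modified intention-to-treat | Contacts, unrestricted |

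**Does another criterion catch the case?** Criteria 1 to 5 concern age and weight, pregnancy, transaminases, haematology and prior TB treatment. Criterion 6 is the nearest: "Rifampin contra-indicated – due to potential drug interactions that are considered too important, or difficult to manage, by health care provider", with allergy or hypersensitivity as the only other ground. Resistance in the source case is not named. Inclusion criterion 3 refers to Canadian or WHO guidelines on eligibility for latent TB treatment, but that concerns treatment in general and states no check specific to rifampin.

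**Who falls in the gap?** The household definition includes anyone who visits the house for 5 hours a week, so many relatives and close friends are already covered. What remains is contacts met only elsewhere.

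**Scale.** Inputs: planned enrolment 1359 and a 35% non-household share (Sample size considerations); rifampin resistance among new cases of 2.4% in Indonesia and 4.1% in Vietnam (exclusion criterion 7). The share of non-household participants who are other contacts is not given; 10% to 50% is assumed.

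- Non-household participants: 1359 × 0.35 ≈ 476
- Low end: 476 × 0.10 × 0.024 ≈ 1.1
- High end: 476 × 0.50 × 0.041 ≈ 9.8

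This gives about 1 to 10 persons exposed to a resistant index case. It is an order of magnitude only. It applies the international figures to all sites, although the Canadian sites plan 100 + 100 + 100 + 150 = 450 of the 1400 listed by site. It also counts resistance that nobody has detected.

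**The case against.** The strongest reply is that this is loose drafting of a rule meant for every contact with an identified index patient. The sub-paragraphs speak of the index TB patients without the word household, the analysis section speaks of contacts in general, and the introductory paragraph on the population does not list other contacts at all. In practice a provider must recommend latent TB treatment before anyone is approached. This has force: the sub-paragraphs are ambiguous, and the broad intent is plausible. But they stand under a criterion that opens with household contacts, and both the closing note and the baseline recording are explicitly limited to that group. If the broad reading was meant, those places do not say so. The provider's recommendation is a practical filter, not a stated resistance check.

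Three stronger conclusions might be inferred, and the documents do not support them.

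- *That the active-TB comparison would be materially distorted.* The 1 to 10 are exposed persons, not TB cases. With the roughly 10% lifetime progression given in the Background, the high end is 9.8 × 0.10 ≈ 1 case over a lifetime, spread over three arms. Recent contacts may progress faster, but the protocol gives no figure for that and no expected number of active-TB cases.
- *That the randomization program lacks a field for the index result in these people.* The baseline case report form is not shown, so this cannot be known.
- *That the primary outcomes are affected.* Completion and drug-related adverse events do not depend on the susceptibility of the infecting strain.

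**Conclusion.** The point holds as a mismatch in scope. By their wording, the exclusion, its note and the baseline recording cover household contacts only; the inclusion criteria admit other contacts; and the analysis section removes contacts generally. The literal result is an eligibility gap for non-household contacts of a known or suspected rifampin-resistant case, and two answers to whether such a person stays in the modified intention-to-treat population.

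The size is unknown and probably small, about 1 to 10 exposed persons under the assumptions shown. The effect on the two primary outcomes is negligible, and no effect on active TB can be quantified from the document. The case rests on participant protection and a consistently defined analysis population. Confidence is high on the literal wording and lower on what the sponsor intended.

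**What to change.** Reconcile inclusion criterion 3, exclusion criterion 7 with its sub-paragraphs and note, the Pre-treatment recording sentence and the modified intention-to-treat paragraph, so that the index-resistance rule, the recording of the index result and the post-randomization exclusion all cover the same contacts. The direct way is to replace the household-contact wording in criterion 7 and in the recording sentence with all contacts, household or other, enrolled because of exposure to an identified index TB patient, and to use the same term in the analysis section. The result would then be recorded for the index patient of every such contact, and the eligibility check at randomization could use it.

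The cost is a wording change and one baseline item collected for all contacts. The downside is that a few non-household contacts whose index result cannot be obtained would not be enrolled. The change would not remove undetected resistance where neither susceptibility testing nor GeneXpert exists, because there the rule accepts contacts of any new case.

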### Rationale for exclusion of children <10 years old and inclusion of children aged 10-17:

There is little published data regarding the pharmacokinetics (PK) of high dose rifampin in children. Therefore, we think it is important to acquire this information in a pediatric population that would otherwise receive doses of treatment based solely on studies in adults.

Previous studies have shown that the metabolism of rifampin is different in young children (under 5 years of age) than in adults. When using standard doses of rifampin, plasma maximum concentrations and AUC were lower among children under five than in older children and adults (Verhagen et al. 2012). The recommended dose for children less than 25kg is therefore 15m/kg/day, with a range 10 to 20mg/kg/day (World Health Organization 2014) , compared to 10mg/Kg for adults. Hence, we think that the population of children under five, for which a higher daily dose (up to double) is already recommended for standard therapy, will not be suitable for this first trial on safety of higher doses of rifampin in LTBI.

In our recently concluded 4R vs 9H studies, of the 422 children enrolled in the 4R arm, 215 were 10 to 17 years old. Among these children, there were no Grade 3-4 adverse events at all with daily rifampin at 10mg/Kg/day (Diallo et al. 2018). Furthermore, adults in the same trial, had significantly fewer Grade 3-5AE with daily rifampin at standard doses compared to those taking daily INH (Menzies et al. 2018). Hence, we believe that the risk of serious adverse events for rifampin at standard dose or at high dose should be lower in children aged 10-17 than in adults. As well, there is published evidence that older children have similar metabolism as adults; therefore WHO recommends adult dosing (i.e. 10mg/kg with maximum 600 mg) for children who weigh 25kg or more (World Health Organization 2014).

There is some published evidence of safety of high dose rifampin among adolescents, although the number of adolescents who were included in these previous studies is very small (Dian et al. 2018; Yunivita et al. 2016). Because older children and adolescents are expected to have metabolism of rifampin similar to adults’, and because no specific side effect was found in the adolescents included in previous studies of TB meningitis (Dian et al. 2018; Yunivita et al. 2016), we believe it is reasonable to include in this study children with age of 10 or older who weigh at least 25kg. This will allow a more thorough assessment of the safety of high dose rifampin in this population, and will provide pharmacokinetic data to establish the ideal dosing.

If the higher doses are shown to be safe and well tolerated in adults and children aged 10 years and older, then we will plan an initial intensive PK study to determine the doses needed in children aged 0-9, followed by a phase 2 study to assess safety in this age group of children, with careful adverse event monitoring.

# Sample size considerations

**For primary outcome of completion:**

We want to detect whether the 2R_20_, and 2R_30_ regimens have superior completion compared to 4R_10_. If the two months regimens do not have significantly superior completion rates, then the rationale to further assess these regimens would be weaker, since the 4R_10_ regimen has the advantages of well documented safety and efficacy.

**Table 2: Sample size required to detect superior completion of 2R_20_ or 2R_30_ compared to 4R_10_**

| Completion rate | | Number required per group to detect significant difference*. | | | |
| --- | --- | --- | --- | --- | --- |
| **4R_10_** | **2R_20_ or 2R_30_** | N per arm – non-HHC | N per arm –HHC | N per arm – mixed | Total N  (3 arms) |
| 70% | 75% | 1248 | 2484 | 2075 | 6226 |
|  | 80% | 290 | 578 | 483 | 1450 |
|  | 85% | 118 | 235 | 196 | 589 |
| **75%** | 80% | 1091 | 2172 | 1815 | 5446 |
|  | **85%** | **247** | ***493*** | ***412*** | ***1237*** |
|  | 90% | 97 | 193 | 151 | 453 |
| 80% | 85% | 903 | 1797 | 1505 | 4515 |
|  | **90%** | 196 | 391 | 306 | 917 |
|  | 92.5% | 115 | 230 | 180 | 540 |

**Power = 80% and alpha = 0.05. The calculation of total number required is based on 3 assumptions: (i) 65% of all enrolled subjects will be Household Contacts (HHC), and 35% will be other risk groups, as was seen in our recently completed 4R trial; (ii) The intra-class correlation coefficient (ICC) or clustering effect of households on completion will be 0.33 – as was demonstrated among study subjects who had at least one other family member in the 4R vs 9H study; (iii) We will use 4 as estimated average number of household contacts, based on two systematic reviews (Morrison J, Pai M, and Hopewll PC 2008; Fox GJ et al. 2013).*

In the 4R vs 9H trials, 78% of adult participants in the phase 2 trial (Menzies D et al. 2008), and the phase 3 trial (Menzies et al. 2018) completed the 4-month regimen. Assuming a similar rate of completion in this planned trial of 75%, then we would need to enroll **412** participants into each arm to detect a 10% better completion rate. Allowing for a 10% withdrawal, or otherwise not analyzable participants, this would inflate the number per arm to 453, so we plan to enroll a total of **1359** participants. As seen above, this number would provide limited power to detect smaller differences in completion. For example, 1815 participants per arm would be needed to detect a 5% better completion rate.

The approximate anticipated number of participants enrolled in each study site is as follows: 100 in Calgary, 100 in Edmonton, 100 in Montreal, 150 in Greater Vancouver (Canada); 500 in Bandung (Indonesia), and 450 in Ho Chi Minh City (Vietnam). Enrollment will be closed when the target 1359 is reached.

**For the primary outcome of safety:** Grade 3-4 Adverse events considered possibly/probably related to study drug:

We want to detect whether the 2R_20_, and 2R_30_ regimens are *not worse* than 4R_10_ in terms of serious adverse events (SAE) that are plausibly related to the study drugs, as defined above. Hence this requires a non-inferiority analysis, and the sample size must be adequate to detect whether the high dose rifampin arms are non-inferior to standard 4R in terms of drug-related SAE.

As shown in Table 3 below, we expect the SAE rate with 4R to be 1% (as seen in the 4R vs 9H phase 3 trial) or 2% (as seen in the 4R vs 9H phase 2 trial), but have also included estimates if the SAE rate is as high as 3%. We define the maximum allowable (maximum tolerated) difference to be **4% more**. (*This is fairly stringent, but we believe a stringent non-inferiority margin is needed, since for an LTBI regimen to be acceptable, it is very important that the regimen is safe. Indeed safety is ESSENTIAL for an LTBI treatment regimen – as these are given to otherwise healthy persons.*) We must account for the clustering effect of households, since, as above, we expect that up to 65% of our participants will be HHC. However, in the just completed 4R vs 9H trial, the cluster effect (or ICC) in terms of serious AE was only 0.05, so the impact on sample size is much less than for completion.

**Table 3; Sample size required to conclude non-inferiority of** **2R_20,_ or 2R_30_ in terms of SAE compared to 4R (***Maximum tolerated difference = 4%)*

| Grade 3-5 Adverse event rate | | Number required per group to conclude non-inferiority. *(Assumes 4 contacts per HH, and ICC = 0.05)* | |
| --- | --- | --- | --- |
| **4R_10_** | **2R_20_ or 2R_30_** | N per arm | Total N – for 3 arms |
|  | | | |
| **1%** | **2%** | **234** | **702** |
|  | 3% | 698 | 2094 |
|  | 4% | 3468 | 10,404 |
|  | | | |
| **2%** | **3%** | **386** | **1158** |
|  | 4% | 1035 | 3105 |
|  | 5% | 4805 | 14,415 |
|  | | | |
| 3% | 4% | 534 | 1602 |
|  | 5% | 1366 | 4098 |
|  | 6% | 6114 | 18432 |

** In this table, for simplicity, all subjects are assumed to be HHC – since the ICC is low and has very modest effect on sample size required.*

Table 3 shows that if SAE rate is only 1% in 4R_10_, and 2% in **2R_20_** or **2R_30_**, then we would need 234 patients per arm, or 702 patients in total to conclude that the high dose regimens were non-inferior to the standard dose for serious adverse events. But, if the real adverse event in the higher dose arms is 3% (ie 2% higher) then we would require 698 per arm, or 2,094 total participants. Hence, we run the risk of not having enough power to conclude non-inferiority if the actual serious adverse event rate is as little as 2% higher. This means we will ‘tolerate’ a very small excess in adverse events. If the actual SAE with **2R_20_** is 4% then the number needed to conclude non-inferiority increases even more markedly. On the other hand, if the SAE rate with 4R is actually 2% (as in phase 2) then the sample size required will be larger. But, with the 1359 anticipated enrolment needed to address our primary objective of completion, we should have adequate power to conclude non-inferiority if the high dose regimens have 3% rate (1% greater occurrence) of serious adverse events.

